## Abstract

**Background:**

Systems psychodynamics provide valuable insights into organizational development. However, to date, instruments that can reliably assess organizations based on systems psychodynamic theories are scarce. The Systematic Multidimensional Organizational Assessment (SyMOA) is a qualitative instrument that provides an in-depth systems psychodynamic analysis of organizational dynamics using a semistructured interview guide. To complement the method, a standardized, quantitative self-assessment questionnaire will be developed and validated.

**Objective:**

The aim of this study is to develop and psychometrically validate an instrument for assessing organizational dynamics based on the SyMOA diagnostic system. The questionnaire is intended to provide a scientifically grounded yet practical diagnostic tool applicable in both research and corporate practice. The findings aim to contribute to the advancement of systems psychodynamic theory and to serve as a foundation for evidence-based interventions in organizational change processes.

**Methods:**

The study follows a multistage development and validation process. First, the SyMOA instrument will be transformed into a questionnaire battery, and the items will be evaluated by experts (expert validity). The items will be tested through factor and item analyses by an online panel (n=150) and iteratively refined. Test-retest reliability will subsequently be assessed in a separate sample (n=150). Finally, factorial and discriminant validity will be examined in a larger validation sample (n=800).

**Results:**

As of February 2026, a first draft of 158 items has been developed based on dimension 1 of the SyMOA framework. The draft has undergone an expert review process with 2 experts in psychodynamics, who provided feedback on content validity and conceptual alignment. Approximately 20% of the items have been revised to improve clarity and theoretical precision. Data collection using a panel started in May 2025 and concluded in late August 2025, with iterative item analysis conducted thereafter.

**Conclusions:**

This study will evaluate the methodological robustness and usability of a questionnaire-based operationalization of systems psychodynamic organizational diagnostics. The anticipated findings are intended to guide further instrument development, normative calibration, and the responsible application of systems psychodynamic approaches in organizational research and practice.

## Introduction

### Background

The increasing complexity, volatility, and emotional demands of modern organizational life have heightened the need for diagnostic approaches that can access not only observable behaviors but also the latent, unconscious dynamics influencing individuals and systems. While conventional organizational diagnostics typically emphasize cognitive, behavioral, or structural dimensions, they often overlook the dynamics that drive behavior beneath the surface [1,2]. Systems psychodynamic diagnostics are a vital and underdeveloped avenue for capturing these phenomena in a scientifically grounded manner.

Rooted in the Tavistock tradition, the systems psychodynamic approach integrates psychoanalytic concepts with open systems theory to analyze how unconscious processes manifest within individuals, teams, and organizational cultures [2-5]. Key concepts include social defense mechanisms, unconscious conflicts, and the projection of anxiety onto systems or structures. These ideas provide a theoretical foundation for understanding phenomena such as resistance to change, dysfunctional leadership dynamics, or behaviors not adequately explained by surface-level assessments.

Despite its conceptual richness, the systems psychodynamic paradigm has historically relied on qualitative methodologies such as organizational role analysis [6], reflective team consultations [7,8], and projective methods such as metaphor elicitation and storytelling [9-11]. These tools offer deep insight but often lack psychometric validation—rendering them less suitable for large-scale organizational research.

On the one hand, organizational practitioners and researchers acknowledge the importance of unconscious dynamics; on the other hand, they lack scalable diagnostic instruments that can reliably quantify such processes while respecting the depth and contextual sensitivity of the systems psychodynamic framework. The challenge lies in designing diagnostics that do not reduce complex unconscious phenomena to simplistic metrics but, rather, operationalize key constructs with theoretical fidelity and psychometric validity.

This study protocol describes the development and validation of a novel psychometric instrument designed to assess unconscious dynamics in organizational contexts: the Systematic Multidimensional Organizational Assessment–Questionnaire (SyMOA-Q). Drawing on both psychodynamic constructs and empirical approaches, the aim is to create a self-assessment questionnaire that is theoretically grounded, methodologically rigorous, and practically useful for both researchers and organizational consultants.

### Prior Work

The SyMOA-Q builds on the authors’ previous work, the Systematic Multidimensional Organizational Assessment (SyMOA; [name] et al, unpublished report), a qualitative systems psychodynamic diagnostic method that assesses organizational dynamics based on 3 dimensions (Table 1). The SyMOA was developed using a theory-to-research approach based on psychodynamic and organizational theories and was refined through an iterative process of theory development, empirical application, and theoretical refinement. It combines the logic of clinical diagnostics based on the *Operationalized Psychodynamic Diagnosis* [12] and organizational research. The SyMOA is a comprehensive and in-depth instrument that captures systemic and psychodynamic aspects within an organization that, to the best of our knowledge, no existing instrument has been able to map so far. A follow-up study testing the quality of the instrument, in particular the intercoder reliability and construct validity, is in preparation [13].

**Table 1. T1:** Systematic Multidimensional Organizational Assessment dimensions.

Dimension	Description
Dimension 1: sociotechnical integration and the organization’s internal level of functioning	The first dimension describes the organization’s understanding of current and past challenges, including its resources and barriers to change. Additionally, this dimension delves deeper beneath the surface to examine the organization’s internal level of functioning. This includes how the organization as a system perceives itself and its environment; how it regulates itself both internally and externally in everyday situations as well as in critical moments; how internal and external communication functions; and how well it establishes bonds both internally among employees and externally with stakeholders such as customers, the market, and supply chains. Furthermore, this dimension captures the defense mechanisms typically used by the organization.
Dimension 2: internal relationship dynamics of the organization	The second dimension assesses the relationship dynamics between different groups within the organization. This includes relationship patterns in typical situations between individual employees, within teams, between teams, between management and stakeholders, and between management and employees.
Dimension 3: unconscious organizational conflicts	On the basis of psychodynamic theories of motivation, emotions, and unconscious conflicts, this dimension conceptualizes the internal conflicts within organizations. Typical conflicts include dependence vs autonomy, control vs subordination, intrinsic vs extrinsic organization-based self-worth conflicts, provision vs self-sufficiency, organizational exploitation vs prosocial engagement, market dominance, and identity conflicts. Conflicts are initially external, rooted in the early history of the company, but over time they become internalized and, thus, develop into unconscious internal conflicts. Conflict represents the clash of opposing positions, the collision of motives, desires, needs, values, and ideas. Conflicts between competing needs are a normal and everyday occurrence, such as between the need for self-determination in the workplace on the one hand and the desire for leadership and guidance on the other. If the underlying conflict is adequately resolved, individuals within the organization can shift flexibly between these needs depending on the situation. However, stress or dysfunction arises when the organization fails to develop an adequate strategy to resolve the fundamental conflict and persistently tries to rigidly implement one pole of these needs. These conflicts are repeatedly triggered by situational factors throughout the organization’s development.

### Research Objectives

Given the predominance of qualitative approaches in systems psychodynamic organizational research and the absence of validated quantitative instruments, this study seeks to develop and examine the psychometric properties of a questionnaire that operationalizes dimension 1 of the SyMOA framework. The objective is to establish an initial measurement model that captures core systems psychodynamic capacities—such as communication, attachment, awareness, and regulation—as perceived by organizational members. By providing a theoretically grounded and empirically testable tool, this study addresses a critical gap in the literature and lays the foundation for subsequent validation of the remaining SyMOA dimensions.

## Methods

### Aim, Design, and Setting

The qualitative methodology of the SyMOA will be converted into a standardized, quantitative self-assessment instrument. This study will first develop and validate a questionnaire for dimension 1 of the SyMOA diagnostics: sociotechnical integration and the organization’s internal level of functioning. The reliability and validity of the newly developed instrument, particularly factorial and discriminant validity, will be determined. A panel will be used for participant recruitment and data collection. The methodological approach of this study follows established best practices in psychometric instrument development and validation, as demonstrated in prior research across diverse applied fields such as health psychology, behavioral assessment, and attitudinal measurement [14-16]. These studies inform the multistage design adopted in this study, including pilot testing, reliability assessment, and factorial validation. The study was initially registered in the Freiburg Register for Clinical Studies (FRKS005727), which is not publicly accessible. It was later additionally registered in the German Clinical Trials Register (DRKS00039410) to ensure public access of the trial record.

### Study Procedure and Measures

The study follows a multistage development and validation process, which is scheduled in 4 phases (Figure 1). However, although data collection spans several months, each participant is involved only briefly, completing the questionnaire once or, at most, twice.

**Figure 1. F1:**
[figure not shown]
Study flow diagram. OPD: *Operationalized Psychodynamic Diagnosis*.

First, the SyMOA scale for dimension 1 will be converted into a set of items and evaluated by 2 experts (expert validity). To this end, a preliminary set of items for the dimension will be created based on the qualitative SyMOA instrument. The aim is to have at least 80 items, which will be answered on a 5-point Likert scale. The items will be presented in German and mostly formulated negatively, with 20% formulated positively. In a second step, the items will be tested using structural and item-level analyses by an online panel sample (n=150) and refined iteratively based on their psychometric performance. Data collection will be conducted via LimeSurvey (LimeSurvey GmbH), a secure web-based survey platform. The development process will be completed if no further adjustment of the items is necessary.

As a third step, the retest reliability will be checked by sending the questionnaire to the same sample as that in the previous round (n=150) after 2 weeks. In a fourth step, a confirmatory factor analysis (CFA) will be carried out to check the fit of the theoretically assumed factor structure based on the SyMOA construct (sample of n=800). In addition, the discriminant validity of the questionnaires will be assessed. For this purpose, existing questionnaires used in clinical practice, such as the *Operationalisierte Psychodynamische Diagnostik–Strukturfragebogen* (OPD-SF) [17], will be used. To be able to assume that the surveyed constructs relate to the organization rather than the person completing the questionnaire, there should be a maximum of moderate correlations. For the evaluation of external validity, employee satisfaction (*Inventar zur Erfassung der Arbeitszufriedenheit* [18]) and work-related quality of life (World Health Organization Quality of Life Scale–Brief [19]) will also be administered in the last round. Although neither scale directly measures the assumed construct of organizational health dynamics, it can be assumed that there is a strong correlation between organizational health and the satisfaction and quality of life exhibited by employees. In addition, sociodemographic data such as age, gender, educational qualifications, professional experience, employment relationship, position or management function, sector, size of the company (eg, number of employees: 30-50 or 50-150), and size of the work area (eg, number of employees: 1-5, 5-10, or 10-20) will be evaluated in relation to the results.

For the development of the questionnaire for T1 to Tx (ie, from the start of data collection to the final item analysis round), as well as for the verification of the test-retest reliability for Tx+1 and the confirmatory sample for Tx+2, the recorded variables and their operationalization are listed in Table 2.

**Table 2. T2:** Data collection with instruments and time point of measurement.

Time point of measurement and measured variable	Operationalization
T1^a^-Tx^b^—development of questionnaire based on dimension 1	
Quality of the items of the scale	Item analysis: item difficulty, item selectivity, item variance, and distribution
Reliability of the scale	Internal consistency of the scale
Tx+1^c^—retest reliability	
Retest reliability	Agreement of the results of Tx+1 with those of Tx
Tx+2^d^—CFA^e^ and validity	
Internal level of functioning of the organization	SyMOA-Q^f^ based on dimension 1 of the SyMOA^g^
Factorial validity of the scales	CFA
Sociodemographic data	Age, gender, educational qualifications, professional experience, employment relationship, position or management function, sector, size of the company (30-50, 50-150, 150-250, 250‐1000, or >1000), and size of work area (1-5, 5-10, 10-20, 20-50, and >50)
Discriminant validity via structural level of employees	OPD-SFK [17]^h^
Employee satisfaction as an external criterion	IAZ^i^ [18]
Work-related quality of life as an external criterion	WHOQOL-BREF [19]^j^

a T1 marks the start of data collection.

b Tx refers to the final round of phase 2 (completion of item analysis).

c Tx+1 indicates the retest reliability assessment (phase 3).

d Tx+2 refers to the confirmatory factor analysis and validity testing (phase 4).

e CFA: confirmatory factor analysis.

f SyMOA-Q: Systematic Multidimensional Organizational Assessment–Questionnaire.

g SyMOA: Systematic Multidimensional Organizational Assessment.

h OPD-SFK: *Operationalisierte Psychodynamische Diagnostik–Strukturfragebogen Kurz*.

i IAZ: Inventar zur Erfassung der Arbeitszufriedenheit.

j WHOQOL-BREF: World Health Organization Quality of Life Scale–Brief.

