### Recruitment and Data Collection

The panel will be used for participant recruitment and data collection. Potential participants are registered users who meet the inclusion criteria. They must be aged ≥18 years, speak German, and be employed. Furthermore, the company with which they work must have at least 30 employees. Illiterate persons will be excluded. A message with the link to the study and the offer to participate will be sent to the database of potential participants until the required subsample of 150 people is reached for the first rounds. For the last round, a sample of 800 persons will be recruited.

Before the study, participants will receive written information about the procedure and any expected risks and side effects and the names of the people to contact. Informed consent will be obtained electronically in advance from the participants who agree to continue with the study.

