#### Statistical Analysis

The quantitative data will be analyzed using SPSS (IBM Corp), R (R Foundation for Statistical Computing), and JASP. The following statistical evaluations will be performed: a CFA (global fit using the chi-square test and goodness-of-fit indexes [root mean square error of approximation<0.05; Tucker-Lewis index and comparative fit index>0.9]), local fit (factor loadings>0.4), iterative item analyses (item distribution and variance, item difficulty [0.2-0.8], and discriminatory power [>0.3]), and verification of correlations and internal consistency of the scales (retest reliability [>0.7] and discriminant validity). The data from the confirmatory sample will also be checked for correlations between variables.

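### The WHOQOL-BREF is labelled work-related quality of life with no work-specific adaptation described, and the strong correlation expected of it sits uneasily with the discriminant argument in the same section

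*Protocol article*

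**What the plan says.** Study Procedure and Measures names two external criteria for the final round. One is employee satisfaction, measured with the IAZ. For the other, the text says that "work-related quality of life (World Health Organization Quality of Life Scale–Brief [19]) will also be administered in the last round". Table 2 lists "Work-related quality of life as an external criterion" with the same instrument beside it, and the table's footnote spells out the name as "WHOQOL-BREF: World Health Organization Quality of Life Scale–Brief".

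The expected result is given once for both criteria: "it can be assumed that there is a strong correlation between organizational health and the satisfaction and quality of life exhibited by employees". It follows a caveat: "Although neither scale directly measures the assumed construct of organizational health dynamics".

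Just before this, the section sets the discriminant expectation. To show that SyMOA-Q describes the organization and not the respondent, its correlations with the OPD structure questionnaire are limited: "there should be a maximum of moderate correlations".

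On analysis, the Statistical Analysis section says only that "The data from the confirmatory sample will also be checked for correlations between variables". Strengths and Limitations lists criterion-related (external) validity among the aspects of validity that the study addresses.

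**The concern.** There are two linked problems.

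1. **The label and the instrument differ.** The variable is called work-related, but nothing in the instrument's printed name refers to work, and no adaptation is described. A report of a link with work-related quality of life would claim more than the measure supports, whatever the size of the correlation.

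2. **The expectation does not separate two readings.** Quality of life, like personality structure, is reported by the respondent about the respondent. The plan treats a high correlation with one such measure as a warning that SyMOA-Q reflects the person. It treats a high correlation with another as support. A strong correlation with the WHOQOL-BREF could mean that organizational functioning affects employees' lives. It could also mean that the same personal outlook colours both sets of answers.

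At stake is what the study can say about one of its two external criteria, in an article that presents external validity as covered.

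**Working it through.** The article gives no expected coefficient, threshold or power for the external criteria, so there is no figure to reproduce. The check is mainly a comparison of the article's own statements.

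**Step 1: label against instrument**

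| Place | Label given | Instrument named |
|---|---|---|
| Study Procedure and Measures, text | work-related quality of life | World Health Organization Quality of Life Scale–Brief |
| Table 2, row | work-related quality of life | WHOQOL-BREF |
| Table 2, footnote | none | same full name, no reference to work |

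The other criterion differs: the IAZ's German title refers to job satisfaction. The mismatch appears in both the text and the operationalization table, so it is not an isolated slip.

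**Step 2: label against hypothesis**

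The sentence that states the expected correlation speaks of quality of life without the work qualifier. The construct in the label is therefore not the construct in the hypothesis.

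**Step 3: the two expectations side by side**

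| Comparison measure | Describes | Expected correlation | Reading intended |
|---|---|---|---|
| OPD structure questionnaire | the respondent | at most moderate | SyMOA-Q is not about the person |
| WHOQOL-BREF | the respondent | strong | SyMOA-Q has external validity |

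The two are not logically contradictory, because personality structure and quality of life are different attributes. But the argument in the first row applies in part to the second, and the article does not say how to tell the readings apart.

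**Step 4: decision rule**

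Statistical Analysis gives cut-offs for model fit, loadings, item difficulty, discriminatory power and retest reliability. It gives none for the external criteria, and the word strong has no number.

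**Step 5: does sampling error matter here?**

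The final round has 800 respondents ("For the last round, a sample of 800 persons will be recruited"). With Fisher's z, SE = 1/√(n − 3) = 1/√797 = 0.0354, and the 95% limits are tanh(atanh r ± 1.96 × 0.0354). The values of r below are illustrative and do not come from the article.

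| Observed r | 95% CI |
|---|---|
| 0.3 | 0.24 to 0.36 |
| 0.4 | 0.34 to 0.46 |
| 0.5 | 0.45 to 0.55 |
| 0.6 | 0.55 to 0.64 |

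Power to show a non-zero correlation exceeds 0.999 even for a true r of 0.2. A bare check for correlation is thus almost certain to find one. What the finding means will depend on what the scale is said to measure and what size was expected, and these are the two points left loose.

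**The case against.** **The scale is conceded to be indirect.** The article admits that neither criterion measures organizational health directly, and its expectation is already worded for quality of life. This stands, and it narrows the first problem to the label. It does not remove it: the caveat concerns the SyMOA-Q construct and does not say that the scale may fail to measure work-related quality of life.

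**The person-level influence can be examined.** The OPD short form is collected in the same round, and Strengths and Limitations names the interplay between person and organization as something the study can assess. That is fair: the data will exist. The article does not, however, connect that assessment to the reading of the quality-of-life correlation.

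**What the scale covers is not in the article.** Reference 19 is not at hand, so the point is not that the scale has been proved unsuitable. It is that the name carries no work qualifier and no adaptation is described. If the full protocol describes one, the article should say so.

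**A stronger reading is tempting.** A reader might infer that the criterion test will probably fail for a perfectly good questionnaire, because quality of life depends on much besides the employer, and that a sound SyMOA-Q would then be judged to lack external validity. The documents do not support this. There is no pass/fail rule to fail, and the true correlation is unknown. Any estimate rests on assumed paths. For example, take SyMOA-Q with work-specific quality of life at 0.5 to 0.7, and work-specific with general quality of life at 0.4 to 0.8. If the whole link runs through the work-specific part, the implied correlation is 0.5 × 0.4 = 0.20 to 0.7 × 0.8 = 0.56. That range spans an equally assumed cut-off of 0.5. At n=800 the chance of observing at least 0.5 is about 0.0002 for a true r of 0.4, 0.50 for 0.5, and close to 1 for 0.6. The assumptions decide the answer.

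**Conclusion.** The point holds as one of labelling and interpretation. In two places the article assigns to the WHOQOL-BREF a construct that, on its own description, the scale is not shown to measure. The single strong expectation for both criteria also leaves a high SyMOA-Q/WHOQOL-BREF correlation open to two readings, one of which the discriminant test in the same section is meant to guard against.

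Its reach is one of the two external criteria and the claim that external validity is addressed. The factor analysis, item analyses and retest reliability are not affected. No numerical bias can be stated. The conclusion rests on the instrument's name as printed and on the absence of any described adaptation; it needs no assumption about the true correlation. It is worth correcting because the remedy is cheap and changes what may be concluded.

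**What to change.** - **Rename the variable** in Study Procedure and Measures and in Table 2 to quality of life (general). If a work-specific adaptation is in fact used, describe it instead.
- **Limit the claim.** In Strengths and Limitations and in later reports, refer to an association with quality of life, not with work-related quality of life.
- **Replace the single expectation with a graded one**, fixed before the data of the n=800 round are analysed: SyMOA-Q should correlate more strongly with the IAZ than with the WHOQOL-BREF. Report both correlations with confidence intervals and compare them with a test for two dependent correlations sharing one variable, such as Williams' or Steiger's. Align the scoring direction first, since most SyMOA-Q items are negatively worded. Say which SyMOA-Q score is used, since Future Directions places scoring at the level of subscale factor scores.

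The cost is wording and one extra calculation on data already planned, with no additional respondents. Exchanging the WHOQOL-BREF for a work-specific scale would be possible but is a preference, not a requirement of this point.
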